#### Peer workers

Data for peer workers facilitating the program will comprise reflective notes on experiences of delivering the program and 30-min interviews conducted at the conclusion of each Honest, Open, Proud course (after the booster session). Peer workers will be asked to keep written or typed notes on their experiences to be submitted for inclusion in the research data at the conclusion of data collection. Interviews will follow a semi-structured protocol, guided by the CFIR constructs, and will be digitally recorded for professional transcription. Willingness to continue participation will be checked with peer workers at each participation occasion. Participation may extend for 6 months from October 2019 and comprise three to four interviews in that period. Facilitation of the program will take approximately 8 h plus preparation time. Estimated research data collection time is approximately 2 h of notes per course (total of 6 h) plus up to 2 h of interview time (30 min per interview).

#### Staff

Data for staff in the settings in which the program will be delivered will comprise one interview of approximately 60 min. Interviews with up to five staff members at each site will follow a semi-structured protocol, guided by the CFIR constructs, and will be digitally recorded for professional transcription. Participation for staff members will be on a single occasion only. Data collection from staff is anticipated to commence late in 2019, after at least one Honest, Open, Proud course has been completed at the site.

#### Administrative data

During study setup, a request for aggregated administrative data on quality, safety and consumer experiences will be made to the data governance bodies of each location. To minimise issues of confidentiality and delays due to complex permissions, these data may be restricted to publicly available reports on performance. The purpose of examining administrative data is to supplement primary data from staff observations of service-level changes and individual participant outcomes.

### Analysis

Quantitative data will comprise program scores of fidelity, overall service scores on measures of safety, effectiveness, patient-centeredness and experience, and individual measures of self-stigma, empowerment, recovery and quality of life. Due to the exploratory nature of the study, it is expected that quantitative data will be primarily descriptive and comprise change scores across time. Where possible, differences between settings and the effects of potential confounds will be tested using multi-level linear models, which will account for clustering of individuals within programs and settings.

All qualitative data will be analysed using a framework approach [32]. Framework analysis, a comprehensive and systematic qualitative analysis method driven by the observations of participants, is particularly appropriate for studies with applied research questions that are concerned with people’s experiences of a phenomenon and the influence of contextual factors. Data will be interrogated for the CFIR constructs [24] (contextual factors) and implementation, service and individual outcomes specified in the conceptual model [21]. The framework will be elaborated with inductive coding of concepts not well-described by the high level dimensions of the model.

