**Methods:**

The project will use an interventional implementation science approach: small-scale, researcher-led implementation of the Honest, Open, Proud program to explore contextual influences, and implementation, service and individual outcomes. The Consolidated Framework for Implementation Research (CFIR) will be used to guide investigation of contextual factors. Implementation outcomes (feasibility, fidelity, acceptability, sustainability) and service outcomes (safety, person-centeredness and effectiveness) will be examined in interviews with a range of staff within the services, checklists of adherence to program protocols and analysis of administrative data. Individual quantitative outcomes will include self-stigma, recovery and quality of life, measured at baseline, end of program and follow-up. Qualitative enquiry will focus on experiences with the peer worker and program.

Quantitative analyses will comprise change scores on service and individual outcome measures. Where possible, differences between settings and the effects of potential confounds will be tested using multi-level linear models, which will account for clustering of individuals within programs and settings. Qualitative data will be analysed using a framework approach, which is an effective way of combining inductive and deductive coding to test and refine a thematic frame.

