### Participants

Study participants comprise three main groups at each setting: peer workers, other staff and people with experience of mental illness.

It is anticipated that approximately eight peer workers will participate, including the three study investigators. All peer workers will be invited to contribute data to the study in the form of reflective notes on their experiences and/or participation in an interview.

Up to five staff members in each setting involved in the peer worker program directly or indirectly will be invited to participate by direct invitation from one of the investigators. During implementation of the program, investigators will develop a list of leadership, clinical and administrative staff at each location who may be able to provide insight into the key implementation issues. Participants will be purposively sampled from these lists to provide a range of views on the five implementation construct domains of the Consolidated Framework for Implementation Research (CFIR) [24].

The third key group is people with lived experience of mental illness. As an exploratory study, no specific sample size calculations have been undertaken for individual outcomes. Based on medium-sized effects observed in previous studies trialling the Honest, Open, Proud program [17], we will aim for a minimum of three groups comprising eight participants per study setting (*n* = 72). Data collected during pilot testing of the intervention will also be included (total *N* = 80).

There are no specific exclusion criteria. However, the program and associated research project measures are all in English and approach the issues from a Western conceptualization of stigma and mental illness. As such, this may prove challenging for people from different cultural or language backgrounds. We will not specifically exclude these people from participating, but they may require extra assistance to take part.

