#### Secondary outcomes

At the service level, outcomes of interest are safety, person-centeredness and effectiveness. These will be investigated via interviews with staff and analysis of administrative data, including quality and safety monitoring, and routine outcome measurement statistics such as service level consumer experience data [e.g. the Your Experience of Service (YES) questionnaire [25]] to assess overall changes to these figures following introduction of the peer workers and program.

Table 2 presents the secondary outcomes at the individual level. These outcomes will be self-stigma, measured by both a specific self-stigma scale [Internalized Stigma of Mental Illness Inventory [26]] and a disclosure scale [Coming Out with Mental Illness Scale [27]], empowerment [Empowerment Scale [28]], recovery [Self-Identified Stages of Recovery [29]], and quality of life [Personal Wellbeing Index [30]]. A brief distress screener [Distress Questionnaire 5 [31]] and personal and clinical characteristics are also included.

**Table 2 Tab2:** Individual level secondary outcome measures

Construct	Measure	No. of Items	Example items	Rating scale
Self-stigma	Internalized Stigma of Mental Illness Inventory [26]	10	For each question, please mark whether you strongly disagree (1), disagree (2), agree (3), or strongly agree (4): “I can have a good, fulfilling life, despite my mental illness”	4-point scale Range: 1 (strongly disagree) to 4 (strongly agree).
Self-stigma	Coming Out with Mental Illness Scale [27]	21	Are you out about your mental illness? (yes = complete page 2, no = complete page 3). Page 2: I came out of the closet to gain acceptance from others. Page 3: In the future I will come out of the closet to gain acceptance from others.	Page 2, 3: 7-point scale Range: 1 (strongly disagree) to 7 (strongly agree).
Disclosure	Individual disclosure items (author-created)	4	Have you disclosed your mental illness to your family and friends? “In general, how distressed or worried are you in terms of secrecy or disclosure of your mental illness to others?”	7-point scale Range: 1 (not at all) to 7 (very much).
Empowerment	Empowerment Scale [28]	28	“I see myself as a capable person” “I can pretty much determine what will happen in my life”	4-point scale Range: 1 (strongly disagree) to 4 (strongly agree).

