#### Program participants

Baseline measures including demographic and limited clinical data will be completed upon recruitment to the study and return of the consent form, prior to commencing the Honest, Open, Proud program. Questionnaires will be available both on tablets managed by the research team (using Qualtrics) and in paper form, according to participant preference. To avoid error introduced by participant management of codes, questionnaires will be identified by participant first name (or pseudonym) and last initial. Participants will be advised about the use of names during the initial contact about the program so that they may elect not to participate if uncomfortable with identified data collection. Names will be removed and replaced by a code after matching of questionnaires is complete. Outcome measures will be completed at the conclusion of Lesson 3 (3 weeks) and again at the conclusion of the booster session (6–8 weeks after baseline).

A brief feedback session (half-to-one hour) will be conducted at the end of the booster sessions to gather additional information on participant experience. People who did not participate in the outcome measurement may elect to participate in the feedback session by completing written informed consent at this point of the study. Participants may take part in a face-to-face discussion or elect to answer the same open-ended questions in a brief, online survey.

Total participation time, including program sessions, outcome measures and the feedback session is approximately 10–12 h across 8 weeks. Data collection is anticipated to commence in October 2019 and be completed early in 2020.

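### Individual outcomes are measured three times but summarised mainly as change scores; fitting the planned multi-level models to all three scores would be a cheap, optional improvement

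*Protocol article*

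**What the plan says.** The protocol article's Analysis section says of the exploratory quantitative work that "it is expected that quantitative data will be primarily descriptive and comprise change scores across time". The Methods paragraph of the abstract says the same: "Quantitative analyses will comprise change scores on service and individual outcome measures". The Analysis section then adds, as a step to be taken if the data allow it, that "differences between settings and the effects of potential confounds will be tested using multi-level linear models". About the structure of those models it gives one detail only, namely the clause "which will account for clustering of individuals within programs and settings". It does not say whether the modelled outcome is a change score or the three repeated scores, and it names no level for occasions within a person.

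On timing, the Program participants section says: "Outcome measures will be completed at the conclusion of Lesson 3 (3 weeks) and again at the conclusion of the booster session". With baseline, that makes three occasions, as Table 3 also shows. On status, the Secondary outcomes section says: "Table 2 presents the secondary outcomes at the individual level". The Participants section states that "no specific sample size calculations have been undertaken for individual outcomes".

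**The concern.** Both later questionnaires are filled in at the end of a session, so someone who does not attend is likely to have no score. A baseline-to-follow-up change score needs the booster questionnaire. A participant who answered at baseline and 3 weeks and then left therefore adds nothing to the follow-up figure, although their 3-week score is the one record showing whether leavers were doing better or worse than those who stayed.

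The study has no control arm in which selective attendance could cancel. If attendance at the booster is related to earlier scores, the mean follow-up change partly reflects who stayed. The Aims section makes impact on individuals part of the second of two primary aims, so these figures will be read even though the measures are labelled secondary.

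**Working it through.** **The plan's own figure.** 3 settings × 3 groups × 8 participants = 72. The stated total of 80 implies 8 pilot participants (72 + 8 = 80). Both figures reproduce. The article gives no attrition rate, correlations or missingness mechanism, so every such input below is an assumption.

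**Why the mechanism matters.** Let Y0, Y1 and Y2 be the scores at baseline, 3 weeks and follow-up, each with SD 1. If staying depends on a recorded quantity Z, the bias in the mean of Y2 − Y0 is roughly Cov(Y2 − Y0, Z) / Var(Z), times the shift in mean Z among those who stay. Take correlations of 0.60 (Y0, Y1), 0.75 (Y1, Y2) and 0.50 (Y0, Y2):
- Z = early change, Y1 − Y0: Cov = 0.75 − 0.50 − 0.60 + 1 = 0.65; Var = 2(1 − 0.60) = 0.80; slope = 0.65 / 0.80 = 0.81. The bias is large.
- Z = 3-week score, Y1: slope = 0.75 − 0.60 = 0.15. The bias is small. With equal correlations the slope is exactly 0.
- Z = baseline, Y0: slope = 0.50 − 1 = −0.50. The bias has the opposite sign.

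**Simulation A.** n = 72, true follow-up change 0.20 SD, roughly 27-31% missing at follow-up, log-odds 0.8 to 1.2 per SD for loss related to early change. The model is maximum likelihood with unstructured covariance on all three scores.

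| Loss depends on | Correlations | Mean change score | Likelihood model |
|---|---|---|---|
| Nothing (random) | 0.60 / 0.75 / 0.50 | unbiased | unbiased |
| Early change | 0.60 / 0.75 / 0.50 | 0.34 to 0.39 | 0.20 |
| Early change | all 0.5 | 0.30 to 0.35 | 0.20 |
| Early change | all 0.7 | 0.26 to 0.29 | 0.20 |
| 3-week score only | all equal | unbiased | unbiased |
| Unseen follow-up score | 0.60 / 0.75 / 0.50 | 0.30 to 0.34 | 0.29 to 0.33 |
| Unseen follow-up score | all 0.5 | 0.30 to 0.33 | 0.34 to 0.38 |
| Unseen follow-up score | all 0.7 | 0.26 to 0.28 | 0.30 to 0.32 |

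The largest bias from recorded-score loss is 0.39 − 0.20 = 0.19 SD. Under random loss the model's standard error is about 4-9% smaller (for example 0.125 against 0.137, and 1 − 0.125 / 0.137 = 9%).

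**Simulation B.** n = 72, equal correlations of 0.5 or 0.7, true changes −0.3 SD at 3 weeks and −0.5 SD at follow-up.
- Random loss (19-36% missing at follow-up): both methods unbiased.
- Loss depending on earlier recorded scores (24-41% missing): change-score bias +0.035 to +0.099; model about 0. Because the true change is negative, this understates improvement, the reverse of the early-change rows in A.
- Loss depending on the unseen score (24-41% missing): change-score bias −0.034 to −0.097; model −0.078 to −0.190.
- Spread of the estimates was nearly the same: 0.102-0.154 for the change score, 0.100-0.155 for the model.

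**Choice of covariance.** With the unequal correlations and loss depending on early change, a model with only a random intercept per person gave 0.26 and 0.28 rather than 0.20. It reduces the bias but does not remove it; the unstructured form does.

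None of these runs included clustering by group.

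**The case against.** The strongest reply is that little here is fixed wrongly. The article calls the quantitative work exploratory and mainly descriptive, the individual outcomes are secondary, and multi-level models are already planned. The clustering levels it names do not rule out a level for occasions. Missing-data rules are commonly left to a full protocol or SAP, so their absence from an article is no finding. All of that stands, and it limits the weight of the point.

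A reader might infer that the plan discards everyone with a missing questionnaire. The article does not support this. It states no complete-case rule, and change over several time points is planned: someone who misses only the booster still has a 3-week change, and someone who misses only the 3-week questionnaire still has a follow-up change.

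A reader might also infer that a repeated-measures model is always less biased. It is not. The advantage holds when loss depends on recorded scores. Under random loss neither method is biased, and when loss depends on the unseen follow-up score the model is no better and can be worse. Absence driven by how people feel at the time of the booster is plausible, since that is when the questionnaire is completed.

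What survives is narrower. Change scores are the stated main summary, the article does not say that the models use the repeated scores, and a follow-up change score leaves the 3-week scores of booster non-attenders unused.

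**Conclusion.** The point holds as an optional improvement to exploratory secondary outcomes. If booster attendance depends on scores already recorded, the mean baseline-to-follow-up change is off by about 0 to 0.19 SD at an assumed 24-41% loss, and the direction varies with the mechanism. A likelihood model with unstructured within-person covariance removes that bias under a missing-at-random assumption. The gain in precision is small at best.

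The range rests on assumed loss rates, mechanisms and correlations, and on simulations without group clustering. It shows what could happen; it does not predict what will. The plan is not invalid as written.

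**What to change.** State in the Analysis section that the planned multi-level linear models will be fitted to the three repeated scores, with:
- occasions within participants within groups;
- an unstructured within-person covariance, not only a random intercept;
- a random effect for group, and fixed effects for time, setting and time-by-setting;
- everyone with a baseline score included.

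Report model-based change at 3 weeks and at follow-up with 95% confidence intervals, and keep raw change scores as a descriptive table. With complete data, the model's time and time-by-setting contrasts equal the change-score contrasts.

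Because the model relies on data being missing at random, also report the number missing at each time point and compare the early scores of booster attenders and non-attenders.

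The cost is a few sentences and slightly more analysis work, with no new data. Two limits remain: with 3 × 3 = 9 main-study groups the group variance will be estimated imprecisely, and the model offers no protection if loss depends on the unseen follow-up score.

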## Discussion

The current protocol describes a study that uses an implementation science approach to evaluate a small-scale implementation of a program in three distinct settings in an Australian context. The primary aim of the study is to evaluate the success of the implementation of the program, with secondary aims to examine other related implementation factors including feasibility, fidelity, acceptability and sustainability of the program, service-level outcomes of safety, person-centeredness and effectiveness of the program, and individual-level outcomes for the effectiveness of the program on aspects such as self-stigma, recovery and quality of life. Peer work can have a positive impact on both consumer outcomes and satisfaction with care, as well as for the peer workers themselves [5–7]. Further, augmenting the workforce with this important and accessible group has strong potential to alleviate substantial burden on the mental health system [3, 4] and improve services’ recovery focus [5–7]. This project will provide critical implementation evidence to ensure the optimal delivery of peer work in the broader Australian mental health system to achieve these benefits.

## Data Availability

Not applicable.

## Abbreviations

ACACIA: The ACT Consumer and Carer Mental Health Research Unit
ACT: Australian Capital Territory
ANZCTR: Australian New Zealand Clinical Trials Registry
CFIR: Consolidated Framework for Implementation Research
NDIS: National Disability Insurance Scheme
YES: Your Experience of Service
